**Table 2 Tab2:** **Complication grades according to the Dindo-DeOliveira classification scheme**
^**a**^

**Grade**	**Definition**
Grade I	Any deviation from the normal postoperative course without the need for pharmacological treatment or surgical, endoscopic and radiologic intervention
Grade II	Requiring pharmacological treatment with drugs other than those allowed for grade I complications
Grade III	Requiring surgical, endoscopic or radiological intervention
Grade IIIa	Intervention not under general anaesthesia
Grade IIIb	Intervention under general anaesthesia
Grade IV	Life-threatening complications requiring intensive care unit management
Grade IVa	Single-organ dysfunction
Grade IVb	Multiorgan dysfunction
Grade V	Death of patient

^a^The Dindo-DeOliveira classification system is reported in detail elsewhere [42,43].

### Methods for avoiding bias

#### Minimizing systemic bias

Patients will be randomized to one of the drain groups during the surgical procedure after resectability of the tumour is confirmed. Randomization will be accomplished using balanced permutation blocks by generation of random numbers in order to obtain homogeneity between groups. Patients scheduled for pancreaticoduodenectomy and distal pancreatectomy will be randomized separately, as these two procedures are different with regard to the course and consequences of POPF [25,44]. Opaque, sealed envelopes will be produced, labelled with the randomization number and containing a sheet that states the group allocation for the patient. Randomization envelopes will be used in consecutive order. Basic characteristics of the patient and the day of randomization will be documented on a data sheet so that compliance to the randomization scheme may be checked retrospectively. If patients are excluded from the study after randomization, their numbers will not be reused. Obviously, operating surgeons, attending physicians and nursing staff cannot be blinded, as the drains look different. However, outcome assessors will be blinded. The randomization process will follow the CONSORT guidelines (Figure 1) [45].

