### Study population and eligibility criteria

The DRAPA trial will encompass two participating centres: University Hospital Hradec Králové and University Hospital Olomouc, both in the Czech Republic. All patients who are scheduled for pancreatic resection at the two participating centres will be screened and assessed for eligibility.

Only patients who undergo pancreaticoduodenectomy or distal pancreatic resection will be included in the study. Patients with nonstandard procedures or a procedure associated with higher morbidity will be excluded from the study to achieve a homogeneous study group. Detailed inclusion and exclusion criteria are described below.

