#### Exclusion criteria

No pancreatic resection performed: nonresectable tumourTotal pancreatectomy, central pancreatectomy or enucleationMultivisceral resectionLaparoscopic procedureResection of the portal vein and reconstruction with a graftLack of compliance, informed consent not provided or refusal to participate

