### Statistical methods

Each patient’s allocation to the analysed population will be defined prior to the analysis and will be documented. In the full-analysis set, patients will be analysed as randomized according to the intention-to-treat principle. The intention-to-treat principle implies that the analysis includes all randomized patients. The per-protocol analysis set will include all the patients without major protocol deviation. Deviations from the protocol will be assessed as major or minor. Patients with major deviations from the protocol will be excluded from the per-protocol analysis. The safety analysis set will analyse patients according to the treatment.

The null hypothesis assumes that the risk of development of POPF and postoperative complications is equal in both groups. A binary logistic regression will be applied in order to compare POPF in the groups adjusting for other factors. Two-tailed *t*-tests or nonparametric Mann–Whitney *U* tests will be applied for continuous secondary endpoints. χ^2^ tests or Fisher’s exact test will be used for analysis of categorical secondary endpoints. A *P*-value <0.05 will be considered statistically significant. Statistical analyses will be performed using NCSS statistical software (NCSS, Kaysville, UT, USA).

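### The envelope may be opened once resectability is confirmed, before some exclusions that depend on the operation performed are settled, and exclusion after randomisation is left unlimited

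*Protocol article*

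**What the plan says.** On timing, the protocol article (Minimizing systemic bias) states: "Patients will be randomized to one of the drain groups during the surgical procedure after resectability of the tumour is confirmed". The same section sets the strata by the planned operation: "Patients scheduled for pancreaticoduodenectomy and distal pancreatectomy will be randomized separately". It also says that "operating surgeons, attending physicians and nursing staff cannot be blinded, as the drains look different".

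On eligibility, Exclusion criteria lists non-resectable tumours, total or central pancreatectomy, enucleation, multivisceral resection, laparoscopic procedures, and resection "of the portal vein and reconstruction with a" graft. Study population and eligibility criteria adds a rule tied to the operation carried out: "Only patients who undergo pancreaticoduodenectomy or distal pancreatic resection will be included in the study".

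On patients who leave after allocation, Minimizing systemic bias says: "If patients are excluded from the study after randomization, their numbers will not be reused". It gives no grounds or limits for such exclusion.

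On analysis, Statistical methods says of the full-analysis set: "The intention-to-treat principle implies that the analysis includes all randomized patients". The only set with a stated exclusion rule is the per-protocol set: "Patients with major deviations from the protocol will be excluded from the per-protocol analysis".

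**The concern.** Confirming that a tumour can be resected is not the same as knowing which operation will be completed. If the plan changes after the envelope is opened, the person who decides the extent of resection, and so whether an exclusion is met, can know the allocated drain. An exclusion made with that knowledge is no longer independent of the arm, and randomisation does not protect the comparison of those who remain.

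The same early opening lets the surgeon know the arm while making the pancreatic anastomosis or closing the stump, the site from which a postoperative pancreatic fistula (POPF) arises. It also lets gland texture and duct diameter, which are collected during surgery, be recorded with the arm known.

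Finally, the article speaks of exclusion from the study in one place and of analysing everyone randomised in another. A team handling a randomised patient whose operation became a total pancreatectomy could point to either. The choice touches the primary endpoint, because that patient has no remnant from which a fistula could arise.

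**Working it through.** The point rests mainly on comparing sections. Arithmetic serves only to judge scale.

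**1. Which exclusions are settled when resectability is confirmed?**
- Non-resectable tumour: settled.
- Lack of consent, and a planned laparoscopic procedure: ordinarily known before.
- Total or central pancreatectomy, enucleation, multivisceral resection, portal vein graft: settled if planned in advance, open if the operation changes during resection.
- The rule that only patients who undergo one of the two study operations are included: certain only once the operation is done.

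So there is a group, of unknown size, whose ineligibility can emerge after allocation. The strata follow the scheduled procedure, so a change of operation can also put a patient in the wrong stratum.

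**2. What happens to such a patient?** Under the eligibility text the patient does not belong in the study. Under Minimizing systemic bias the patient may be excluded from it, and the number is not reused. Under Statistical methods the patient is in the full-analysis set. The article does not say which governs.

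**3. Does the allocation need to be known earlier?** In Study treatment, nothing described before the drains are placed depends on drain type. The envelope can be opened later without altering any earlier step.

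**4. Scale: lost sample.** Inputs from Sample size calculation: POPF 35% and 17.5%, α 5%, power 80%, 97 per group, 15% dropout, 223 in total.
- The plan's figure first. Arcsine formula, two-sided: n = 2[(1.960 + 0.842)/h]², with h = 2·asin√0.35 − 2·asin√0.175 = 0.403. This gives 96.7, so 97. The two-sided pooled formula gives 99 and the unpooled 95.3. The one-sided pooled formula gives 78, so the article's one-sided label does not reproduce 97. That is a separate matter, and two-sided power is used here.
- Total: 2 × 97 × 1.15 = 223.1.
- If the whole allowance were lost: 223 × 0.85 = 189.6, about 94.8 per arm.
- Power = Φ{[0.175√n − 1.960·√(2 × 0.2625 × 0.7375)] / √(0.35 × 0.65 + 0.175 × 0.825)}. At n = 97: 79.6%. At n = 94.8: 78.6%. The loss is one percentage point.

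**5. Scale: bias.** The document gives no inputs, so this is illustration only. Assume a true POPF risk of 35% in both arms and exclusions in one arm only. If a fraction f is excluded, with risk r among those excluded, the observed risk is (0.35 − f·r)/(1 − f).
- f = 0.05, r = 0.5: 34.2%, a fall of 0.8 points.
- f = 0.10, r = 0.5: 33.3%, a fall of 1.7 points.
- f = 0.10, r = 0.7: 31.1%, a fall of 3.9 points.
- f = 0.15, r = 0.7: 28.8%, a fall of 6.2 points.
- Any f, r = 0.35: no change.
- f = 0.10, r = 0 (for example, total pancreatectomy): 0.35/0.90 = 38.9%, a rise of 3.9 points.

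The sign depends on who is excluded, and the size on assumed fractions and risks. Neither can be fixed from the document.

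**The case against.** The strongest reply has four parts.

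- **The order of events is inferred.** The article gives an earliest point for randomisation, not the moment the envelope is opened, and patients enter by scheduled procedure, so operations planned from the start as ineligible are screened out. This stands: only late changes of plan are at issue, and the trial flowchart, which is not available here, may bear on the order. But the text permits opening before these exclusions are settled.
- **The texts can be read together.** The sentence on exclusion after randomisation is conditional and may be only a numbering safeguard. It could cover withdrawn consent. On this reading a late-ineligible patient stays in the full-analysis set and leaves only the per-protocol set. This also stands. A reader might infer that the two rules cannot both be followed; the documents do not support that. What remains is that the article never says this reading is the intended one.
- **No reason is given why drain type should influence the extent of resection.** That is fair, and arm-dependent exclusion is a possibility, not something shown. The case for a later opening is that it removes the possibility at almost no cost.
- **Technique is standardised.** Anastomosis and stump closure are prescribed, stents and reinforcement are ruled out, and an experienced senior surgeon performs or supervises each operation. This limits performance bias but does not remove it. Splenectomy, for instance, is left to the surgeon and determines whether a second drain is placed in distal resection.

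**Conclusion.** The point holds as a weakness in the timing of randomisation and in the wording on later exclusions. It should be fixed, but it does not invalidate the plan. The article lets allocation become known to an unblinded surgeon before some exclusions need be settled, and it does not limit removal from the study after that.

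The conclusion rests on one inference: that in some patients the final operation is not certain when resectability is confirmed. The number of such patients is unknown.

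Two stronger readings are not supported. A reader might infer a spurious difference of some 2 to 4 percentage points in POPF. That needs an exclusion fraction, exclusion in one arm only and a raised risk among those excluded, none of which the document gives, and for total pancreatectomy the direction reverses. A reader might also infer a material loss of sample. One point of power is negligible, and the article does not break down its 15% allowance, so it cannot be attributed to these exclusions.

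**What to change.** 1. In Minimizing systemic bias, have the envelope opened only after the resection and the anastomosis or stump closure are complete and every intraoperative exclusion criterion has been checked and recorded, immediately before drain insertion. Take it from the stratum of the procedure performed, not the one scheduled.
2. Reword the sentence on exclusion after randomisation: a patient found ineligible after allocation keeps the number, stays in follow-up and in the full-analysis set as randomised, and leaves only the per-protocol set.

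The cost is a short amendment and an eligibility check before the envelope is opened. No extra staff or procedures are needed, and no surgical step changes. Recruitment is under way according to Trial status, so the amendment should come soon. Patients already randomised keep their allocation, and the second change can cover them too. The later opening does not address unblinding of staff after surgery, which is outside this point.

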**Figure 1 Fig1:**
[figure not shown]
Flowchart of the process of the phases of the randomized trial according to the CONSORT guidelines.

#### Minimizing treatment bias

Pancreatic resection is standardized in both participating centres. Both types of drain are used in the participating departments; all surgeons participating in the study are familiar with them. Insertion of both types of drain is a simple, common procedure performed on a routine basis, which eliminates a learning curve.

#### Minimizing measurement bias

Detection and grading of POPF and postoperative complications, which are the primary and secondary endpoints, will be based on data in the patient’s record form. Blinding is not necessary, because the occurrence of POPF is an objective endpoint that cannot be influenced by the patient. Physician blinding is not possible, because the drains are apparently different.

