### Postoperative data collection

A daily visit of the study patients will be made by clinical investigators or a delegated physician. All protocol-required information collected during the trial will be entered into the patient’s record form. Preoperative data gathered include patient sex, age, body mass index, American Society of Anesthesiologists physical status classification system score and comorbidities, especially those considered to increase the risk of POPF (diabetes mellitus and ischaemic heart disease) [35,36]. Intraoperative data to be collected include surgery duration, estimated blood loss, diameter of the main pancreatic duct and pancreatic gland texture. The diameter of the main pancreatic duct will be measured with a set of probes. Postoperative data to be gathered include volume of the drain output measured every 24 hours, amylase content analysed every other day starting on day 3, and the day of drain removal. Laboratory tests will include serum amylase, C-reactive protein, bilirubin and leukocyte count on days 3 and 7 [37]. Postoperative course assessments will include duration of intensive care, hospital stay including readmissions for postoperative complications, reinterventions (reoperations, endoscopy and interventional radiology procedures) and the reasons for readmissions. All the patients will have undergo ultrasonography or computed tomography (CT) before discharge from the hospital to detect any fluid collections. The patients will be seen by a clinical investigator 6 weeks and 3 months after the surgery in the outpatient department.

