### Primary and secondary endpoints

The primary endpoint of this study is the rate of POPF occurrence. POPF is defined by the ISGPF as any measurable volume of drain fluid on or after postoperative day 3 with amylase content greater than three times the normal upper serum value [6]. Three grades of POPF are determined according to clinical severity: A, B and C.

Grade A POPF, also called ‘transient fistula’, has no clinical impact. The patient’s clinical condition is good, and little or no change in clinical management is required. Hospital discharge is not delayed. The drains are usually removed within 3 weeks.

Grade B POPF is symptomatic and clinically apparent, and peripancreatic collections may occur. Changes in clinical management are required, such as nutritional support, as well as antibiotics in cases of infection, and new drains into the collections may be inserted. Hospital stay is usually delayed, or readmission may be required.

Grade C POPF is severe and clinically significant. The clinical condition of the patient is poor, and stability may be borderline. Major changes in clinical management are required, such as intensive care, CT-guided drainage of peripancreatic collections or reoperation.

The secondary endpoint is the postoperative morbidity, including wound infection, intraabdominal collections, delayed gastric emptying, postoperative haemorrhage, pneumonia, abdominal rupture, cardiac events and neurological complications (Table 1), as previously defined [5,30,38-41]. Postoperative complications are graded based on severity according to the Clavien-Dindo definition as modified by DeOliveira and colleagues for pancreatic surgery [42,43] (Table 2).

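### The article promises blinded outcome assessors in one place and calls blinding unnecessary in another, for a reason that does not cover staff who see the drain; the exposure lies mainly in fistula grade and complications

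*Protocol article*

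**What the plan says.** Blinding is addressed twice in the protocol article, under Methods for avoiding bias.

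- **Minimizing systemic bias.** "Obviously, operating surgeons, attending physicians and nursing staff cannot be blinded, as the drains look different". The next sentence reads "However, outcome assessors will be blinded".
- **Minimizing measurement bias.** This section names the record form kept for each patient as its source: "Detection and grading of POPF and postoperative complications, which are the primary and secondary endpoints, will be based on data". Then: "Blinding is not necessary, because the occurrence of POPF is an objective endpoint that cannot be influenced by the patient". Then: "Physician blinding is not possible, because the drains are apparently different". Blinded assessors do not appear in this section.

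Two other sections bear on the point.

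- **Primary and secondary endpoints.** "The primary endpoint of this study is the rate of POPF occurrence", with no restriction by grade. Occurrence is a laboratory criterion. In addition, "Three grades of POPF are determined according to clinical severity: A, B and C".
- **Postoperative data collection.** "A daily visit of the study patients will be made by clinical investigators or a delegated physician". The section does not say who completes the record form.

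**The concern.** The section that ought to say who classifies the endpoints says that blinding is not needed. The section on randomization says that assessors are blinded. A site could follow either and believe it was following the protocol.

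The reason offered also misses the risk. That a patient cannot alter drain amylase says nothing about clinicians, who by both sections know the allocation. The article itself reports, under Objectives and hypothesis and again in the Discussion, that some surgeons regard suction drains as hazardous and suspect that negative pressure promotes fistula. Prior belief on the tested question is therefore acknowledged among the profession.

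At stake is whether POPF grade and complications, which carry the clinical interpretation of the trial, are classified by people who know the drain type, and whether the final report can truthfully describe the assessment as blinded.

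**Working it through.** The article states no figure on this point, so the check is a comparison of its sections.

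**1. Are the two statements compatible as written?**

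| Group | Minimizing systemic bias | Minimizing measurement bias |
|---|---|---|
| Patients | not mentioned | endpoint said to be beyond their influence |
| Surgeons, physicians, nurses | cannot be blinded | physicians cannot be blinded |
| Outcome assessors | blinded | not mentioned; blinding called unnecessary without qualification |

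The sections agree on treating staff. On assessors, one makes a commitment and the other makes a general statement that, taken literally, withdraws it.

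**2. Does the stated reason support the statement?** Only for patients. The sentence opens a subject (detection and grading of both endpoints) in which the people who act and record are clinicians, and it gives no reason why their knowledge of the drain would be harmless.

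**3. Which endpoints can unblinded staff affect?**

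- *Any-grade POPF (primary).* It requires drain amylase above three times the upper normal serum value on or after day 3. Under Study treatment, sampling starts on day 3 and repeats every other day while the drain is in, so scheduled samples fall on days 3, 5, 7 and so on. Without POPF, the drain comes out within a window of days 4 to 6. Removal on day 4 leaves one scheduled sample (day 3). Removal on day 6 leaves two (days 3 and 5). Removal on day 5 leaves one or two, depending on the order of events that day. Every patient managed to protocol has the day 3 sample; what staff can affect is mainly whether the day 5 sample exists.
- *POPF grade.* Grades A, B and C are separated largely by what clinicians do: nutritional support, antibiotics, new drains, timing of discharge, readmission, intensive care, reoperation. These are decisions of staff who see the drain.
- *Table 1 complications.* Several turn on a treatment decision: pneumonia and urinary tract infection (antibiotics), symptomatic fluidothorax (evacuation), delayed gastric emptying (nasogastric tube), abdominal rupture (resuture). Others are closer to measurement, such as biliary leak by bilirubin ratio.
- *Clavien-Dindo grade.* Table 2 sets most grades by the intervention or level of care given.

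**4. What can masked classification remove?** It removes the influence of knowing the allocation when a grade or diagnosis is assigned from the record. It cannot undo a drain removal, antibiotic course or delayed discharge already decided by someone who knew the drain type.

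The exposure is therefore small to moderate for the primary endpoint and larger for grade and morbidity, and masking reaches only part of it.

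**The case against.** The strongest reply is that there is no contradiction. The disputed sentence says the endpoint cannot be influenced by the patient, and the next one turns to physicians. Read as a pair, they say that patients need not be blinded and physicians cannot be. The other section adds that assessors are. All three then fit together, and basing detection and grading on the record form suits blinded assessors working from records.

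This reading is possible, but the text does not state it. The sentence is unqualified, stands in the section on measurement, and is not tied to the assessors promised elsewhere. If only patients are meant, a few words would settle it. The reply therefore lowers the seriousness of the point without removing it.

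Two further replies stand in full. The primary endpoint is largely a laboratory result, and disagreement over A, B or C does not change whether a POPF occurred. Masking also cannot correct management chosen by unblinded staff.

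A reader might infer more than the article supports:

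- *That the primary endpoint is assessed open-label.* The article commits to blinded assessors, and the amylase rule leaves limited room for judgement.
- *That unblinded ward staff complete the record form.* This is plausible from the daily visits but is not stated.
- *That the false-positive rate is raised by a calculable amount.* This would need a size for the artefactual difference between arms, and the article contains none.
- *That the article fails by not describing how masking is done.* A condensed article may leave that to the full protocol. The point here is the conflict between two statements it does make.

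**Conclusion.** The two sections on blinding are not reconciled, and the reason given for dispensing with blinding does not address influence by staff who see the drain. The consequence falls mainly on POPF grade, the Table 1 complications and the Clavien-Dindo grade. It falls much less on any-grade POPF, where the main route is whether a day 5 sample exists.

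No numerical size can be given from the documents. The conclusion assumes that the record form shows or implies the drain type unless it is masked, and that the disputed sentence is not silently restricted to patients. If it is so restricted, the defect is one of unclear wording and of leaving the assessors out of the section where they matter.

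This should be corrected, but it ranks below a defect that must be fixed for the trial to be valid: a commitment to blinded assessors is already in the text, and the primary endpoint rests mostly on a laboratory threshold.

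**What to change.** 1. In Minimizing measurement bias, replace the sentence that calls blinding unnecessary. If it was meant for patients only, say so.
2. State in the same section that the blinded outcome assessors already promised under Minimizing systemic bias classify POPF occurrence, POPF grade and complication grade; that they work from a record-form extract in which drain type and allocation are masked; and that their classifications are the ones analysed.
3. Acknowledge that this protects the classification step only. Sampling, drain removal and treatment remain decisions of unblinded staff, and the report should say so when interpreting grade and morbidity.

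The change needs no additional patients, procedures or roles, since the assessors are already foreseen. The cost is rewording and clerical time to prepare masked extracts. Because recruitment is under way, it is best made early: cases already graded by someone aware of the drain type would have to be classified again.
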